# Study protocol for a multicenter randomised controlled trial on the (cost)effectiveness of biopsy combined with same-session MR-guided LITT versus biopsy alone in patients with primary irresectable glioblastoma (EMITT trial)

**DOI:** 10.1186/s12885-023-11282-7

**Published:** 2023-08-23

**Keywords:** Glioblastoma, Laser ablation, Laser therapy, Ablation, Brain neoplasms, Magnetic resonance-guided laser-induced thermal therapy

## Abstract

**Background:**

Glioblastoma (GBM) is the most common primary, malignant brain tumour with a 5-year survival of 5%. If possible, a glioblastoma is resected and further treated with chemoradiation therapy (CRT), but resection is not feasible in about 30% of cases. Current standard of care in these cases is a biopsy followed by CRT. Magnetic resonance (MR) imaging-guided laser interstitial thermal therapy (LITT) has been suggested as a minimally invasive alternative when surgery is not feasible. However, high-quality evidence directly comparing LITT with standard of care is lacking, precluding any conclusions on (cost-)effectiveness. We therefore propose a multicenter randomized controlled study to assess the (cost-)effectiveness of MR-guided LITT as compared to current standard of care (EMITT trial).

**Methods and analysis:**

The EMITT trial will be a multicenter pragmatic randomized controlled trial in the Netherlands. Seven Dutch hospitals will participate in this study. In total 238 patients will be randomized with 1:1 allocation to receive either biopsy combined with same-session MR-guided LITT therapy followed by CRT or the current standard of care being biopsy followed by CRT. The primary outcomes will be health-related quality of life (HR-QoL) (non-inferiority) using EORTC QLQ-C30 + BN20 scores at 5 months after randomization and overall survival (superiority). Secondary outcomes comprise cost-effectiveness (healthcare and societal perspective) and HR-QoL of life over an 18-month time horizon, progression free survival, tumour response, disease specific survival, longitudinal effects, effects on adjuvant treatment, ablation percentage and complication rates.

**Discussion:**

The EMITT trial will be the first RCT on the effectiveness of LITT in patients with glioblastoma as compared with current standard of care. Together with the Dutch Brain Tumour Patient association, we hypothesize that LITT may improve overall survival without substantially affecting patients’ quality of life.

**Trial registration:**

This trial is registered at ClinicalTrials.gov (NCT05318612).

**Supplementary Information:**

The online version contains supplementary material available at 10.1186/s12885-023-11282-7.

## Introduction

Glioblastoma (GBM) is the most common and most malignant primary brain tumour [1]. These tumours account for around 60% of all primary brain tumours in adult patients with an incidence ranging from 3.9 to 4.17 per 100.000 persons [2]. GBMs are in most cases highly debilitating and often occur at a relatively young age (median 59 years) [3]. Although many efforts have been made to improve current therapies, patients with GBM face a poor prognosis, with a 5-year survival of 5% [4, 5]. Current standard of care includes surgical resection followed by adjuvant chemoradiation therapy (CRT) [6]. This strategy has been associated with median overall survival (OS) of 14.5–18.5 months, depending on the extent of resection [7, 8]. However, in 30% of patients surgery appears not to be feasible [9], most often due to the unfavourable location of the tumour, and sometimes because the patient does not desire surgical resection due to the possible complications and/or risk of further deterioration. These patients miss the benefit of surgical resection since biopsy followed by CRT results in a faster decline in quality of life and a median survival ranging from 5 to 9.4 months [10]. Laser-induced thermal therapy (LITT) (also referred to as Stereotactic Laser Ablation (SLA)), has been developed as a minimally invasive treatment for tumours, including brain tumours [11]. A recent systematic review, consisting of phase I and II studies, showed that the median survival in patients with newly diagnosed irresectable glioblastoma who received LITT is 10.2 months [12]. No data regarding the quality of life of patients who have undergone LITT is available. To date, no randomized controlled clinical trials looking at the effectiveness of LITT in patients with newly diagnosed irresectable glioblastoma have been published. A search on clinicaltrials.gov, ISRCTN Registry and EU clinical trials register for (ongoing) trials identified no (planned) randomized studies investigating the role of LITT in patients with newly diagnosed irresectable glioblastoma, precluding any conclusions on (cost-)effectiveness.

A preceding pilot study at Radboudumc [13] including 15 patients of which 10 treated with LITT showed that patients with an irresectable glioblastoma are willing to participate in a randomized trial. In addition, safety and feasibility data are acceptable and in line with previous reports [11, 14].

Given the potential survival benefit but lack of evidence to support LITT, we will conduct a multicenter randomized controlled trial to evaluate effectiveness of this technique in patients with primary irresectable glioblastoma (EMITT trial). It is expected that addition of LITT will yield longer survival without substantially affecting patients’ quality of life. Only when the survival is superior and the quality of life is non-inferior in the intervention group compared to the control group, LITT will be considered effective. Furthermore, due to the increasing pressure on healthcare budgets, cost-effectiveness of LITT will also be assessed.

## Methods

### Study design

The EMITT trial is designed as a multicenter pragmatic randomized controlled trial. Patients will be randomized with 1:1 allocation to receive either biopsy followed by adjuvant chemotherapy and/or radiation which is the current standard of care (control group), or biopsy combined with same-session MR-guided LITT therapy followed by adjuvant chemotherapy and/or radiation (intervention group). The trial is registered at www.clinicialtrials.gov (NCT05318612).

### Study setting

Seven Dutch hospitals will participate in this trial (Appendix 1). Six of the seven hospitals are academic hospitals, one hospital is a non-academic hospital. Biopsy combined with same-session LITT therapy will be performed in two designated and trained centers, namely the Radboud university medical center (Nijmegen) and the University Medical Center Utrecht (Utrecht). Biopsy alone will be performed at all including participating centers. Adjuvant treatment will be given either in the including center or in a local hospital in the patient’s own region.

### Study population

Patients with a suspected diagnosis of glioblastoma will be discussed at their local multidisciplinary tumor board meeting. When the board advises biopsy only due to the unfavorable location of the tumor, or if the patient wishes no resection, the subject is potentially eligible for this study. The local participating neurosurgeon will then discuss the case with the centralized study expert panel. This will be done by sharing anonymized, necessary clinical and radiological information through a safe digital environment. The expert panel consists of three neurosurgeons, involved in the trial. The expert panel will review all information to judge if the patient is a potential candidate for LITT according to the inclusion criteria. An overview of in- and exclusion criteria is provided in Table 1. When eligible, the patient will be informed about the study by one of the members of the study team both orally and in writing through the patient information form (PIF). After a mandatory reflection period of 48 h, the patient will be called by one of the researchers and will be asked whether he or she wishes to participate in the study. After having obtained written informed consent, the patient will be formally included in the study and will be randomized.

**Table 1 Tab1:** Overview of in- and exclusion criteria

Inclusion criteria	Exclusion criteria
• Suspected glioblastoma	• Pregnancy
• Supratentorial localization of the tumor	• Contraindication for general anesthesia or MRI
• Age over 18 years	• Final diagnosis other than glioblastoma
• Patient is not amenable for surgical resection • Karnofsky Performance Status > = 70	• Insufficient command of the Dutch language by the patient or a family member, making it impossible to fill in the questionnaires

#### Glioblastoma

Whenever the term “glioblastoma” or “GBM” is used in this protocol, it refers to all WHO grade 4 gliomas of the new 2021 classification [12]. Therefore, this includes:

Glioblastoma, IDH wildtype, WHO grade 4;Diffuse hemispheric glioma, H3,3 G34-mutant, WHO grade 4;Diffuse midline glioma, H3 K27M-mutant, WHO grade 4;Astrocytoma, IDH-mutant, WHO grade 4.

### Randomization and study groups

Randomization will be performed by one of the study physicians using randomized permuted blocks of 4 and 6 through a web-based module (CastorEDC) which is available 7 days a week, 24 h per day. The randomization sequence is concealed and cannot be altered or predicted during the study. Assignments will be balanced in a 1:1 ratio between the two study arms, stratified by center. In the intervention arm, a maximum number of patients treated by each of the LITT centers will be set to 63 to avoid an uneven distribution of patients over the two LITT centers and to share the patient load.

Randomization will be done pre-operatively. It is not deemed feasible to randomize peri-operatively, since LITT requires specific hospital resources (staff, specific operation room and MRI time) which will need to be planned in advance and preferably within two weeks. The study will be open due to practicality and logistic reasons since patients from the intervention group need to be referred to one of the two LITT centers.

After inclusion, the patient will undergo biopsy or biopsy combined with same-session LITT within a maximum of 3 weeks.

### Intervention group

Patients will be admitted the day before the procedure and neuronavigation imaging will be performed. An ablation plan will be made based on the navigation MRI, where one or more trajectories are designed to optimize coverage of the lesion shape while avoiding intervening structures, where planned coverage should be at least 70%.

Patients will receive 4 mg dexamethasone the day before surgery and 8 mg from the day of surgery onward to reduce post-operative edema. Dexamethasone will be phased out after surgery.

LITT procedures will be performed by for LITT trained neurosurgeons. The neurosurgeons who perform LITT in this trial should have performed at least 5 proctored LITT procedures before they are allowed to carry out the procedure independently. The procedure will be performed under general anesthesia. Through a short skin incision, a small twist-drill burr hole and durotomy are performed. Stereotactic biopsy will be performed conform routine procedure using Brainlab neuronavigation and Varioguide™ arm (BrainLAB AG, Feldkirchen, Germany). In the LITT group, frozen section analysis will be performed to confirm diagnosis. If pathological analysis may suggest another diagnosis than a glioma, LITT will not be performed, and the procedure will be terminated.

Upon confirmation of glioma diagnosis, the laser fibers will be inserted and secured with a skull anchor screw. The patient will be transported to the MRI suite where the cooling lines and laser fiberoptic are connected through a waveguide to the control room. Pre-treatment T1-weighted images are acquired to verify the position(s) of the probe(s). For treatment monitoring, MR thermometry images are continuously acquired during laser delivery. LITT will be delivered using a CE-marked MR-guided LITT system for neurosurgical application. Currently, the Visualase Thermal Therapy System (Medtronic, USA), used in this trial, is the only available certified system in Europe for neurosurgical ablation. A Medtronic representative will be present during LITT procedures for technical support. At the end of treatment, contrast-enhanced T1-weighted imaging after intravenous gadolinium injection are acquired. The bone anchor, applicator, and head frame will be removed, and the wound will be sutured.

In case of significant bleeding after biopsy (volume of the hematoma larger than the volume of the tumor on the navigation MRI or diameter of the hematoma larger than 30 mm), the ablation will not be carried out in the trajectory where the bleeding occurred and, if applicable, will only be carried out in the remaining trajectories if the expected total ablation rate is still greater than or equal to 70%.

### Control group

Patients will be admitted the day before surgery and neuronavigation imaging will be made. All neurosurgeons in all participating centers will be allowed to perform this procedure in the context of the trial. Biopsy will be performed under general anesthesia conform local routine procedure. After biopsy, the procedure will be ended. Patients in the control group will not receive additional dexamethasone as part of the trial.

#### Adjuvant treatment

Adjuvant radiotherapy and/or chemotherapy will be prescribed according to the EANO guidelines in both study groups [6].

### Outcomes

#### Primary endpoints

Primary outcomes will be overall survival (superiority), and health-related quality of life (non-inferiority) measured at 5 months after randomization using the scores of the EORTC QLQ-C30 + BN20 questionnaire [15, 16].

#### Secondary endpoints

Secondary outcomes will be healthcare costs using iMCQ and iPCQ questionnaires, (generic) health-related quality of life using the Eq. 5D-5 L and the EORTC QLQ C30 + BN20 questionnaires filled in at different time points during the entire duration of the study, progression free survival (defined as no radiological tumour growth) and tumour response by evaluating follow-up MRI scans, disease specific survival, longitudinal effects, effects on adjuvant treatment, ablation percentage and complication rates.

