### Follow-up

In both arms, follow-up will comprise standard of care, i.e., follow-up visit every 3 months with an MRI at 3 and 6 months and later if clinically relevant. Patients will be followed until one of the following events occurs: (i) death; (ii) end of study (max 64 months after start of inclusion) is reached; or (iii) patient withdraws informed consent. Quality of life questionnaires (EORTC QLQ-C30 + BN20 and EuroQol 5D-5 L) will be completed at baseline, < 72 h after surgical procedure, monthly for the first six months from randomization, subsequently at 12 and 18 months after randomization and thereafter yearly up to a maximum of 64 months [15–17]. Resource use and productivity losses will be measured monthly for the first six months from randomization, subsequently at 12 and 18 months after randomization and thereafter yearly up to a maximum of 64 months, using the iMTA Medical Consumption Questionnaire (iMCQ) and iMTA Productivity Cost Questionnaire (iPCQ) [18, 19]. Questionnaires will be filled in online through a secure web-based module, if necessary, with the help of a relative or caregiver. Adverse events will be monitored using the questionnaires and electronic patient files.

A detailed study flowchart is outlined in Fig. 1.

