#### Secondary outcomes

Cox proportional hazard analysis (two-sided) will be performed to evaluate the difference in progression-free and disease-free survival between groups. Kaplan-Meier estimates will be used to assess progression-free and disease-free survival.

Additional Cox proportional hazard analysis will be performed on overall, disease-specific, and progression-free survival measured from time of treatment, KPS and tumor size. Tumor volume response will be calculated as mean differences with 95%CIs. Complications will be calculated as rate difference with 95%CIs. Generic HR-QoL effects will be calculated as mean differences between groups with 95%CIs. Longitudinal effects will be assessed using mixed model analysis. Effects on adjuvant treatment will be calculated as proportions not completing CRT and mean differences in duration of CRT course with 95%CIs.

To assess the cost-effectiveness, an economic evaluation will be performed from both a healthcare and a societal perspective, adopting a 1.5-year time horizon. Costs will be calculated according to the Dutch guideline for economic evaluation, by multiplying resource use with the corresponding unit costs. Average costs will be calculated in both groups and differences will be calculated inclusive of 95% confidence intervals. Effectiveness will be measured in terms of quality-adjusted life years (QALYs). QALYs will be based on the utility scores as measured with the EQ-5D-5 L, using the Dutch tariff and the area under the curve method. If relevant, incremental cost-effectiveness ratios (ICERs) will be calculated by dividing estimated differences in costs by differences in QALYs. Uncertainty will be addressed by means of non-parametric bootstrapping and where relevant one-way sensitivity analyses are performed.

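### The stated definition of progression-free survival counts only radiological growth and leaves out death; the analysis text also writes disease-free where disease-specific survival is the listed endpoint

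*Protocol article*

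**What the plan says.** The Secondary endpoints section of the protocol article lists "progression free survival (defined as no radiological tumour growth", to be judged, like tumour response, on the follow-up MRI scans, and then "disease specific survival, longitudinal effects, effects on adjuvant treatment, ablation percentage and complication rates". The abstract gives the same pair of survival endpoints: "progression free survival, tumour response, disease specific survival". The parenthesis is the only definition of PFS in the article. Death appears elsewhere only as a reason for follow-up to end, and its role in PFS is not given.

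The imaging schedule, under Follow-up, is "follow-up visit every 3 months with an MRI at 3 and 6 months and later if clinically relevant".

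The analysis, under Statistical methods, Secondary outcomes, reads "Cox proportional hazard analysis (two-sided) will be performed to evaluate the difference in progression-free and disease-free survival between groups", and then "Kaplan-Meier estimates will be used to assess progression-free and disease-free survival". Disease-free survival is not listed or defined as an outcome anywhere. The next paragraph of that section plans a further Cox analysis, timed from treatment, and there names overall, disease-specific and progression-free survival.

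**The concern.** Taken literally, the PFS definition makes growth on a scan the only event. A patient who dies before any scan shows growth has failed, but contributes no failure. In a standard Cox or Kaplan-Meier analysis such a patient would ordinarily be censored at death or at the last scan. Censoring of that kind is treated as uninformative, which is hard to defend when most deaths are expected to come from the same tumour.

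This matters more here than in most trials. Expected survival is short, only two follow-up scans are scheduled, and the design assumes that deaths come at half the rate in the LITT arm. The number of failures lost would then differ between the arms, and the result would not be what readers understand by progression-free survival.

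A second, smaller point is that the main between-group analysis names an endpoint that is not in the list. Disease-free survival has no natural starting state in patients whose tumour is not resected, and disease-specific survival is left without a main analysis under its own name.

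**Working it through.** **Inputs**
- Median overall survival m: 5.1 months (control) and 10.2 months (LITT), from Sample size, Overall survival.
- Exponential survival, S(t) = exp(−ln 2 · t / m): the form used in Sample size, Quality-of-life.
- Scheduled MRI at 3 and 6 months, from Follow-up.
- 119 patients per arm, from Final sample size.

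**Step 1. Reproduce the plan's own survival figures.** At t = 4.5 months:
- Control: exp(−0.6931 × 4.5 / 5.1) = 0.542.
- LITT: exp(−0.6931 × 4.5 / 10.2) = 0.7365.

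The plan states 54.2% and 73.6%, so the model is the plan's own.

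**Step 2. Deaths before each scheduled MRI, 1 − S(t).**

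| Scan | Control | LITT | Of 119 per arm |
|---|---|---|---|
| 3 months | 1 − 0.665 = 33.5% | 1 − 0.816 = 18.4% | about 40 vs 22 |
| 6 months | 1 − 0.442 = 55.8% | 1 − 0.665 = 33.5% | about 66 vs 40 |

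**Step 3. What these figures measure.** Patients who die before 3 months have had no scheduled follow-up scan, so growth could be documented only on an unscheduled one. The 6-month row is an upper bound on deaths without documented growth by that time, because some of these patients will have shown growth at 3 months.

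**Step 4. Sensitivity to the time origin.** Step 2 starts survival and the scan schedule at the same moment. The plan's quality-of-life calculation instead treats 5 months after randomisation as about 4.5 months after intervention. If scans are timed from randomisation and the survival clock starts 0.5 months later:
- By the first scan (t = 2.5): 1 − exp(−0.6931 × 2.5 / 5.1) = 28.8% and 1 − exp(−0.6931 × 2.5 / 10.2) = 15.6%.
- By the second scan (t = 5.5): 52.6% and 31.2% by the same formula.

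The picture is unchanged.

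**Step 5. Illustration of deaths without detected growth.** The article gives no progression rate, so this step rests on assumptions outside it: latent progression with a median of 3 to 8 months, independent of death, and MRI every 3 months throughout. By simulation, 50% to 69% of controls and 31% to 50% of LITT patients die without scan-detected growth. This shows the order of size only.

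**Step 6. Disease-free against disease-specific.** The abstract and Secondary endpoints list disease-specific survival. The Cox and Kaplan-Meier sentences say disease-free. The additional Cox analysis says disease-specific. Two listings and one analysis agree, and only the two main analysis sentences differ.

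**Step 7. Does either endpoint drive the sample size?**
- Overall survival: (1.960 + 1.282)² / (0.25 × 0.6931²) = 87.48 events; 87.48 / 0.96 = 91.1, against 91 stated.
- Quality of life: 52 / 0.542 = 96 per arm; 96 / (0.95 × 0.95 × 0.90) = 118.2, hence 119 per arm and 238 in total.

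Neither calculation uses PFS or disease-specific survival.

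**The case against.** The strongest reply is that the parenthesis may only say what kind of progression counts (radiological, not clinical), while the endpoint's name implies that death is a failure. Event and censoring rules are commonly left to a full protocol or analysis plan, and neither is shown. Part of this stands: the article states no censoring rule. A reader might infer that deaths are to be censored as progression-free, but that is the usual consequence of the definition and not an instruction in the text. The reply does not remove the point, because the article does not leave PFS undefined. It gives a definition, and an analysis plan that counted death would depart from its words.

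A reader might also infer that both secondary survival analyses are wrong as written. The text does not support this for the second endpoint: disease-specific survival is named correctly in the next paragraph, so disease-free is most plausibly a slip and not a plan to analyse another endpoint.

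Three further limits are fair.
- The percentages in step 2 are all deaths before a scan date, not deaths without growth, and no bias in a PFS hazard ratio has been derived. The imbalance between arms presupposes the hoped-for hazard ratio of 0.5. With equal survival the loss would be equal, though still present.
- Nothing in the article makes PFS key support for the survival claim. The Introduction ties effectiveness to overall survival and quality of life alone.
- Replacing Kaplan-Meier by cumulative incidence for disease-specific survival is a methodological preference. A Cox model that censors competing deaths has a valid cause-specific reading, and the article gives no rate of other-cause death.

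**Conclusion.** The point holds in limited form. The stated PFS definition omits death, and if it is followed in the planned analyses, patients who die without documented growth have no event. On the plan's own medians and exponential survival, about 33.5% of controls and 18.4% of LITT patients would die before the first scheduled MRI (28.8% and 15.6% if the survival clock starts half a month after randomisation). By 6 months the figures are at most 55.8% and 33.5%. The loss is large, and unequal under the design hypothesis. The exact number affected cannot be derived, because the article gives no progression rate and unscheduled scans are possible.

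The disease-free wording is an internal inconsistency, apparently a slip. Both endpoints are secondary, so the co-primary analyses and the sample size of 238 stand. The change should be made, but it does not threaten the trial's main conclusion.

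**What to change.** 1. In Secondary endpoints, define PFS as time from randomisation to radiological progression or death from any cause, whichever comes first.
2. In Statistical methods, Secondary outcomes, change disease-free to disease-specific in both the Cox and the Kaplan-Meier sentence, so that the listed endpoint has its main between-group analysis under its own name.

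Both are wording changes plus the coding of one endpoint. They need no extra patients or MRI scans and no change to the sample size. Dates of death are needed for overall survival in any case.
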